Participants randomized to TF-CBT will receive a brief 3-session intervention provided within 72 hours after the accident. In this treatment, the patient is instructed to systematically expose him/herself to the fearful memory of the event and stay in this memory until the anxiety has attenuated. By doing this exposure repeated times, the association between the memory and fear response is hypothesized to be gradually extinguished. The placebo group will receive sham treatment i.e. written information about PTSD and how to treat it but without any therapist-guided interventions.

We will measure PTSD symptoms using the Clinician Administered PTSD Scale (CAPS; the gold standard for PTSD assessment) and Posttraumatic Diagnostic Scale,[^22^](#_ENREF_22)^,^[^23^](#_ENREF_23) depression using the Montgomery Åsberg Depression Rating Scale – Self rated (MADRS-S),[^24^](#_ENREF_24) quality of life using the EQ-5D[^25^](#_ENREF_25) and treatment side effects using the Safety Monitoring Uniform Report Form (SMURF)[^26^](#_ENREF_26) at baseline (i.e. before treatment allocation), 2-, 6-, 12-, 24-, 48- and 120 months using blinded assessors. Primary endpoint is set to 6-months after the trauma. Patients unable to come to the clinic for follow-up assessments will be interviewed via telephone or skype.

The primary outcome (significant PTSD symptoms assessed by the CAPS) will be analyzed using risk ratios and numbers-needed-to-treat with 95% confidence intervals. Continuous data will be analyzed in a mixed-effects model adjusting for data attrition (covariance and residual structure will be set based on the best model fit of the data) using intention-to-treat design. Effect sizes for continuous measures will be estimated using Cohen´s *d*. Assessor´s blindness will be also tested (each assessor will guess treatment allocation for each participant and this will be tested in a logistic regression with guess as independent variable and allocation as dependent variable). A flowchart of the treatment study is shown in the attached figure.

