1.2.3 SIDE EFFECTS PROCEDURES

An Adverse Event (AE) in this trial is any untoward medical occurrence regardless of its causal relationship with TF-CBT. AE is assessed at each clinician visit using the SMURF and is classified by the investigator as mild, moderate or severe:

- **Mild:** Acceptable. The subject is awareness of symptoms or signs, but they are easy tolerated.
- **Moderate:** Disturbing. The AE is discomfort enough to interfere with usual daily activity.
- **Severe:** Unacceptable. The subject is unable to work or to do usual daily activities (e.g. death, life-threatening, significant incapacity).

If the AE is regarded as severe, it will be defined as a Serious Adverse Event (SAE). SAEs will be reported in detail to Socialstyrelsen (responsible for side effects in psychological treatments) and will also be stored in the CRF.

Additionally, each AE is to be classified with Assessment of Causality (stored in the CRF):

- **Unlikely:** The event is most likely related to an aetiology other than TF-CBT.
- **Possible:** A causal relationship is conceivable and cannot be dismissed.
- **Probably:** Good reason and sufficient documentation to assume a causal relationship.

If an SAE is at least possibly related to TF-CBT treatment, then it is also to be classified by the investigator as expected or unexpected. An unexpected SAE is defined as a Suspected Unexpected Serious Adverse Reaction (SUSAR). It is expected if it is already known from earlier CBT trials or is mentioned in relevant documents. This will also be directly reported to Socialstyrelsen with follow-up information describing the outcome of the SAE and action taken will be reported as soon as it is available.

In addition, three interim analyses will be conducted by KTA to ensure that the TF-CBT group is not associated with any significant worsening of symptoms. Thus, we have taken extensive steps in order to monitor and record any possible side effects associated with TF-CBT.

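### The side-effect form is scheduled with the CAPS under the same blinded assessors and with no safeguard against disclosure, which puts the blinding of the 6-month primary rating at risk

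*Protocol*

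**What the plan says.** Methods 1.1 (Overall design and procedure) names the CAPS, the Posttraumatic Diagnostic Scale, the MADRS-S, the EQ-5D and, in the same sentence, "treatment side effects using the Safety Monitoring Uniform Report Form (SMURF"), and has all of them measured "at baseline (i.e. before treatment allocation), 2-, 6-, 12-, 24-, 48- and 120 months using blinded assessors". It then states "Primary endpoint is set to 6-months after the trauma". The outcome at that time is caseness on the clinician-administered scale: "The primary outcome (significant PTSD symptoms assessed by the CAPS").

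Methods 1.2.3 (Side effects procedures) ties the same form to clinician contact: "AE is assessed at each clinician visit using the SMURF and is classified by the investigator as mild, moderate or severe". An adverse event is "any untoward medical occurrence regardless of its causal relationship with TF-CBT". In addition, "each AE is to be classified with Assessment of Causality (stored in the CRF"), with classes defined against TF-CBT; the lowest reads "The event is most likely related to an aetiology other than TF-CBT". The investigator is named for severity and for the expectedness of serious events. Nobody is named for causality.

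On protecting the blind, Methods 1.2.1 covers envelopes, the decoding list, concealed block size and code breaking. Methods 1.1 adds an allocation guess by each assessor for each participant, tested by logistic regression.

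**The concern.** Patients cannot be blinded here. One arm has three therapist-led exposure sessions and the other has written information with no therapist. The primary outcome is a clinician's rating, so the assessor's blindness is its main protection against rating bias.

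A question about side effects of treatment is a natural occasion for a patient to mention the sessions, or the lack of them. A causality judgement against TF-CBT also raises the question of whether TF-CBT was given. As written, the protocol places the side-effect form with the assessors who must stay blind, starting at a visit four months before the primary rating, and leaves the causality grader open. If the rater learns the arm and expects TF-CBT to work, caseness may be rated lower in the TF-CBT arm, higher in the control arm, or both, with no true effect behind it.

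**Working it through.** **1. What the protocol fixes and what it leaves open.**

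- CAPS and SMURF share visits and are both assigned to blinded assessors (Methods 1.1).
- The month-2 SMURF falls before the month-6 primary CAPS (Methods 1.1).
- No order of instruments within a visit is given, so at month 6 the SMURF may precede the CAPS.
- No separation between the CAPS rater and the person who takes the SMURF is written in Methods 1.1, 1.2.1 or 1.2.3.
- No instruction to patients about disclosure is written.
- It is not stated whether the same assessor sees a patient at months 2 and 6, or whether the month-6 rater sees earlier safety records.
- The causality grader is not named (Methods 1.2.3).

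There are therefore two routes to disclosure. One lies within the month-6 visit and needs only that the SMURF comes before the CAPS. The other runs from month 2 to month 6 and needs the same rater or shared records. The protocol excludes neither.

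**2. The sample size, used as an input.** For d = 0.3, two-sided 5% and 80% power, the normal approximation gives 2(1.960 + 0.842)²/0.3² = 174.4, so 175 per arm. The t-test version gives 175.4, so 176 per arm and 352 in total. The stated figure is reproduced.

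**3. Illustration of size.** The inputs are 176 per arm (Methods 1.1), a true caseness of 20% in both arms (an assumption, using the rate in the Abstract and Introduction 1.1), and no true effect. The documents give neither a rate of unmasking nor a size of rating bias, so both are assumed.

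If a share u of an arm is unmasked and ratings of those patients shift by a relative amount b, average caseness in that arm is 20% × (1 ± u × b). The chance of a significant result at two-sided 5% is

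Φ(−1.96 + z) + Φ(−1.96 − z), with z = |p₁ − p₂| / √[(p₁(1 − p₁) + p₂(1 − p₂))/176].

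| Assumption | TF-CBT v control | Expected RR | False-positive rate |
|---|---|---|---|
| u = 0.25, b = 0.20, TF-CBT arm only | 19% v 20% | 0.95 | 5.6% |
| u = 0.25, b = 0.10, both arms in opposite directions | 19.5% v 20.5% | 0.95 | 5.6% |
| u × b = 0.05, both arms | 19% v 21% | 0.90 | 7.6% |
| u × b = 0.10, both arms (such as u = 0.5, b = 0.20) | 18% v 22% | 0.82 | 15.6% |
| u × b = 0.15, both arms | 17% v 23% | 0.74 | 29.2% |

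For 18% v 22%: SE = √[(0.1476 + 0.1716)/176] = 0.0426, z = 0.04/0.0426 = 0.939, and Φ(−1.021) + Φ(−2.899) = 0.154 + 0.002 = 0.156.

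For 19% v 20%: SE = √[(0.1539 + 0.1600)/176] = 0.0422, z = 0.237, and Φ(−1.723) + Φ(−2.197) = 0.042 + 0.014 = 0.056.

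The range runs from close to nominal to several times nominal, and nothing in the documents says where in it the trial would fall.

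**The case against.** A reader might infer that the schedule necessarily reveals allocation. The documents do not support that.

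- The SMURF is also taken at baseline, before there is any treatment to discuss, and adverse events are recorded whatever their cause. Both fit a general event inventory. The form itself is a cited source and not at hand, so whether its questions draw out talk of sessions is unknown.
- The same sentence covers a self-rated depression scale, so the phrase about blinded assessors need not mean that one person interviews for every instrument.
- The month-2 route needs the same rater or shared records at month 6, and neither is stated.

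A reader might also take Methods 1.2.3 to require every event to be attributed to TF-CBT, or to have the CAPS rater make that judgement. It requires a classification, of which unlikely is one option, and it assigns the classification to nobody. Masked trials grade relatedness without unmasking. Methods 1.2.1 implies that the treating psychologist knows the allocation, so staff outside the blind already exist.

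The size is fairly contested too. The larger false-positive rates assume sizeable average shifts across both arms. They also reflect all unblinding of the rater, although a patient could disclose the arm in the CAPS interview with no SMURF at all.

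These objections stand against any claim of certainty and against treating the figures as estimates. They do not remove the gap: the protocol gives the side-effect form to the assessors who must stay blind and states nothing to stop disclosure. The guess test measures the damage afterwards. Who collects what, and in what state of blinding, is trial conduct and not a matter for an analysis plan.

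**Conclusion.** The point holds as a risk to blinding that the protocol leaves uncontrolled, not as a demonstrated break of the blind. It rests on three things in the text: CAPS and SMURF are scheduled together under blinded assessors from month 2, the two arms are easy for a patient to tell apart, and no role separation, visit order or non-disclosure instruction is written. The unnamed causality grader adds to the gap but does not show that a CAPS rater is unblinded.

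The size cannot be derived from the documents. Under the assumptions shown, the false-positive rate goes from about 5.6% under mild unmasking to about 16% if average caseness shifts to 18% v 22%. These figures show why the safeguard is worth having; they do not predict the trial's error rate. The change is inexpensive and protects the primary rating, so it should be made.

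**What to change.** In Methods 1.1:

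- At every visit, score and lock the CAPS and record the allocation guess before any side-effect question is asked.
- Have the SMURF taken by existing study staff who do not rate that patient's CAPS. Failing that, use a patient-completed form that the CAPS rater does not see.
- Withhold earlier safety records from the CAPS rater. Order within a visit does not close the month-2 route by itself.
- Tell patients at the start of each visit not to mention what they received.

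In Methods 1.2.3, assign causality grading to an investigator who does not rate the CAPS.

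The cost is protocol wording, form order and some visit logistics. A second interviewer is preferable to self-completion, because Introduction 2.2.1 gives the lack of systematic side-effect data in the previous trial as one reason for this one. A self-completed form may be less complete and need a clarifying call from staff who do not rate the CAPS. What is recorded and reported as an adverse event does not change.

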**1. IS TF-CBT AN EFFECTIVE TREATMENT IN PREVENTING THE DEVELOPMENT OF PTSD SYMPTOMS?**

1.1 OVERALL DESIGN AND PROCEDURE

The design is a randomized controlled trial, where patients in the emergency department who have experienced a traumatic event according to the A-criteria in the DSM-5 (e.g. car crash, rape), are randomized to receive either TF-CBT or to placebo. The placebo group will receive basic written information about PTSD and how treat these symptoms. Thus, the rationale for the placebo arm is to provide the patient with a sham treatment to rule out any major placebo effects. Given the estimated effect sizes in the previous trial by Rothbaum et al. we would need 352 patients (176 in each group) in order to detect a standardized effect size (Cohen´s *d*) of 0.3 (*p* = .05, 80% power). We also want to include additional 10 participants in the beginning of the trial just to test the study procedures.

Exclusion criteria are the following: a) Do not want to participate in the study, b) Ongoing intoxication (e.g. due to alcohol), c) Low cognitive capacity, d) Other serious psychiatric comorbidity (ongoing psychotic symptoms or symptoms from bipolar 1, suicidal ideation)

We will screen all trauma patients at Traumacentrum Karolinska (about 1500 patients per year). Psychiatric interviews will be conducted by a licensed psychologist at the emergency department or any related clinic (e.g. if the patient has been transferred to another clinic). Patients who fulfill the A-criterion in DSM-5 (i.e. they have experienced a highly stressful event threatening physical or psychological integrity) will be asked to participate in the study. Informed consent will be delivered both as written text as well as explained by the study personnel. Baseline assessments (shown below) will then be conducted.

After the patients have signed the informed consent and completed the baseline assessments, they are randomized to either TF-CBT or placebo. Block randomization will be done beforehand by an independent party (Karolinska Trial Alliance; KTA) on an 1:1 ratio.

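### The planned test of assessor blinding cannot by itself separate unblinding from efficacy, because the assessors who guess also rate the symptoms that TF-CBT is meant to reduce

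*Protocol*

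**What the plan says.** Section 1.1 (Overall design and procedure) has CAPS, the other symptom scales and the side-effect form completed at baseline and at every follow-up, the last of these at "48- and 120 months using blinded assessors". On the time point it says "Primary endpoint is set to 6-months after the trauma", and the primary outcome is significant PTSD symptoms on CAPS.

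The check on the blind is in the same section: "each assessor will guess treatment allocation for each participant and this will be tested in a logistic regression with guess as independent variable". The outcome of that model is the allocated arm. The protocol gives no other check. It does not say at which visit the guess is made, whether it comes before or after the CAPS interview, whether a reason is recorded, or how the result will be read. Section 1.2.1 (Blinding and code breaking) deals with envelopes, the decoding list and emergency code breaks only.

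The arms differ in a way patients can see. TF-CBT is three therapist-led sessions. The comparator is written information "without any therapist-guided interventions".

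**The concern.** With a binary guess and a binary allocation, the logistic regression is a test of association in a 2×2 table, and it does not matter which variable is called dependent. Two quite different mechanisms produce that association:

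- **Disclosure.** The patient or another source reveals the arm.
- **Inference from outcome.** The assessor sees a patient who is well and guesses TF-CBT, or one who is unwell and guesses the comparator. If TF-CBT works, these guesses are right more often than chance although the blind is intact.

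The regression cannot tell the two apart. A trial with a real effect and a sound blind could be described as unblinded. A non-significant result is also weak evidence that the blind held if disclosure was limited to a few patients in one arm. The primary outcome is an interviewer rating, so what the trial can credibly say about its blind affects how far that rating is trusted.

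**Working it through.** **Inputs from the protocol, section 1.1.** "we would need 352 patients (176 in each group"), d = 0.3, significance level 0.05, power 80%, allocation 1:1. For the caseness scenarios, the Introduction (section 1.1) gives about 20% developing PTSD, and 20–30% of trauma-care patients at the site with symptoms that warrant treatment.

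**Assumed, because the protocol is silent.** The share of guesses that follow symptoms, the rate of disclosure, and complete follow-up. The test is taken as two-sided.

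**Step 1: the plan's own figure.** n per arm = 2(1.960 + 0.842)²/0.3² = 174.4, so 175 by the normal formula. The t-test version gives 175.4, so 176 per arm and 352 in total. The stated size reproduces.

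**Step 2: method.** Let p₁ and p₀ be the probabilities of guessing TF-CBT in the two arms, Δ = p₁ − p₀, n = 176 and p̄ = (p₁ + p₀)/2. With s₀ = √[2p̄(1 − p̄)/n] and s₁ = √[(p₁(1 − p₁) + p₀(1 − p₀))/n],

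P(significant) = Φ[(|Δ| − 1.96s₀)/s₁] + Φ[(−|Δ| − 1.96s₀)/s₁].

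Simulating the Wald test of the log odds ratio (40,000 runs) agreed to about one percentage point and rejected in 4.9% of runs under the null.

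**Step 3: blind intact, d = 0.3.** Suppose a share w of guesses follows a median split of symptoms and the rest are coin flips. Then p₁ = wΦ(0.15) + (1 − w)/2, with Φ(0.15) = 0.560, and p₀ = 1 − p₁. For w = 1: Δ = 0.1192, s₀ = 0.0533, s₁ = 0.0529, and (0.1192 − 0.1045)/0.0529 = 0.28, which gives 61%.

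| Share of guesses following symptoms | p₁ vs p₀ | Significant |
|---|---|---|
| 100% | 0.560 vs 0.440 | 61% |
| 75% | 0.545 vs 0.455 | 39% |
| 50% | 0.530 vs 0.470 | 20% |
| 25% | 0.515 vs 0.485 | 9% |

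If instead every guess follows PTSD caseness, a shift of 0.3 SD turns 20% into Φ(−0.842 − 0.3) = 12.7%, and 30% into Φ(−0.524 − 0.3) = 20.5%. The guesses are then 87.3% vs 80.0% (significant in 46%) and 79.5% vs 70.0% (54%).

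**Step 4: real disclosure, other guesses random.** If a share u discloses, p₁ = 0.5 + u/2. The other arm has p₀ = 0.5 if only TF-CBT patients disclose, and 0.5 − u/2 if both arms do.

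| u | TF-CBT arm only | Both arms |
|---|---|---|
| 10% | 16% | 47% |
| 20% | 47% | 97% |
| 30% | 82% | >99% |

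**Step 5: can the size of the association separate the two?** Only when it is large. Disclosure by 10% of both arms with random guessing otherwise gives 0.5 + 0.05 = 55.0% correct. An intact blind with 75% of guesses following symptoms gives 54.5% correct. These cannot be told apart with 352 guesses, where the 95% half-width is about 1.96√(0.25/352) = 5 points.

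**Step 6: fewer assessed.** With 141 per arm (80% of 176, assumed), the 61% in step 3 becomes 52%, and the 47% for 10% disclosure in both arms becomes 39%.

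**The case against.** The strongest reply is that the protocol gives a data item and a model and no more. It states no timing and no verdict rule, so a guess made before CAPS is compatible with the text. Timing, reason codes and interpretation are often left to the CRF or the SAP, which is not shown. This stands as far as it goes: their absence alone would be no finding. But the protocol did choose the test, and no later reading of that test separates efficacy from disclosure. The reason for a guess has to be captured at the visit and cannot be recovered in analysis.

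Second, the two kinds of error rest on different guessing models. Step 3 lets guesses follow symptoms; step 4 makes them random. That is correct. If all guesses follow a median split and 10% of TF-CBT patients also disclose, p₁ = 0.10 + 0.90 × 0.560 = 0.604 against 0.440, and the test is significant in 87% of trials. Under the 20% caseness model it is 60%. So with symptom-based guessing the test mainly lacks specificity. Low power belongs to small, one-arm disclosure with otherwise random guesses.

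Third, a reader might infer that a false alarm is certain if TF-CBT works, that a partly broken blind goes unnoticed, or that the check can never be informative. The documents support none of these. The false-alarm rate can be as low as 9%, disclosure by 20% of both arms is detected in 97% of trials, and a very strong association, such as 80% correct against about 56% under full symptom-based guessing, would point to disclosure. Assigning TF-CBT to 80–87% of patients, as the caseness model does, is also an unlikely guessing pattern in a 1:1 trial.

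**Conclusion.** The point holds in this form: the stated regression of allocation on guess cannot by itself separate unblinding from efficacy. With an intact blind and d = 0.3, it is significant in about 9% to 61% of trials as the share of guesses following symptoms rises from 25% to 100%, and in 46–54% if all follow caseness. With random guessing otherwise, its power is about 16% and 47% for disclosure by 10% and 20% of the TF-CBT arm alone; larger or two-arm disclosure is usually detected. The range rests on assumed guess-following shares and disclosure rates and on full follow-up.

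A reader might go further and infer that the protocol would declare the blind held after a non-significant result, or that the primary CAPS comparison is biased. The protocol states no such rule and gives no disclosure rate, and the check does not enter the primary analysis. The contrast between therapist sessions and a text makes disclosure plausible, but that is inference. This is a cheap improvement to a supporting check, not a flaw in the primary analysis.

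**What to change.** At the 2- and 6-month visits:

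- Record the assessor's guess before any CAPS item is asked, with a 'don't know' option.
- Record the reason with a code: patient disclosed, other information, clinical impression, no idea.
- Record separately any disclosure that occurs during the interview.

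Report guesses and disclosures by arm with a blinding index and its confidence interval. Judge the blind from disclosures and from guesses based on other information, not from the regression p-value. The regression can stay as a descriptive summary.

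Excluding and imputing ratings made after a disclosure should not be part of the required change. It would remove data on the basis of a post-randomisation event that may differ between arms, and would lean on 2-month ratings that may be unblinded too and on self-report from patients who know their treatment. At most, show the 6-month result by recorded disclosure as an exploratory sensitivity analysis.

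The cost is a few CRF items and slightly longer visits. No extra staff or patients are needed, and the primary analysis does not change. If the SAP or CRF already fixes the timing and reason of the guess, only the reading of the test needs to be stated.

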1.2 DETAILED METHODOLOGCAL QUALITY PROCEDURES

1.2.1 BLINDING AND CODE BREAKING

We will use sealed envelopes which will be kept safe and accessible only to persons authorized to unblind. A decoding list containing the treatment codes will be kept at the clinic. Randomization allocation for each participant will be made available only after signed consent. Block size of each randomization will be blinded to investigators by KTA. The circumstances under which the code may be broken to other than the treating psychologist are life-threatening emergencies. Any broken code will be logged with name, signature, date, the number of the participant concerned and reason for breaking the code on the code envelope.

